#### Economic analysis

A secondary objective of this study is to assess the cumulative direct and indirect costs associated with each treatment approach and to calculate the incremental cost-effectiveness ratio per clinically meaningful change in cartilage structure (dGEMRIC). The following methods can be used to assess direct and indirect costs associated with each treatment arm. Participants will be asked for consent to researchers linking their study data to various administrative data sources (state, federal and private health insurance databases). To assess direct costs, data on healthcare utilisation over the study period (including hospital admissions, emergency presentations, primary care utilisation and pharmaceutical claims records on subsidised prescription medicines) will be extracted for all consenting participants. Health services and prescription medications will be costed using market prices for the most recent financial year [60–62].

Information on indirect costs associated with each treatment arm will be assessed at baseline, 6 and 12 months using a survey based on the modified World Health Organisation Health and Work Performance Questionnaire (WHO HPQ). The WHO HPQ is a validated tool [38] designed to assess three domains of work performance (absenteeism, presenteeism and critical incidents), as well as basic demographic and occupational information. Participants will be asked to report their annual pre-tax income. As questions relating to income are known to have high rates of missing data, participants will also be asked to report the category of their main job (e.g. executive, service, labourer). Where annual income data are found to be missing, mean salaries for each category of employment can be imputed from the Australian Bureau of Statistics average weekly earnings data [63]. Cost estimates for lost productivity will be conducted according to previously described methods [64]. The survey will also include several questions to capture information on direct costs not obtainable through data linkage, such as outpatient physiotherapy in the public sector and non-subsidised over the counter medication utilisation.

### Sample size

Sample size calculations for the primary outcome are based on statistical power of 90%, and two-sided significance of 5% significance level. With a sample size of 54 patients in each group, we expect to detect a difference of at least 50 ms between two study groups at 12 months based on a standard deviation (SD) of 80 ms for the dGEMRIC index [65, 66]. 50 ms was chosen as clinically significant based upon increased risk of subsequent total hip replacement [67].

Previous research identified an R^2^ ≈ 0.2–0.3 between indirect external measures of hip joint loading and hip neck bone density in people with hip OA, when two covariates (weight and height) were included, indicating a moderate relationship between biomechanical and structural measures. We expect higher R^2^ values, given that we have direct estimates of cartilage stress and strain. Being conservative, however, in order to achieve an R^2^ > 0.2 between cartilage loading stimulus and dGEMRIC scores (with three covariates), a power of 90%, and a two-sided significance level of 5% we require a total of 56 patients at each site. We will, therefore, aim to recruit a total of 140 participants for the study to allow for a drop-out rate of 20%, including 5% cross over to the surgical group.

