### Outcomes

The primary outcome measure for analysis will be the 12-month change in the average T_1_ relaxation time, assessed with dGEMRIC, for a ROI comprising both acetabular and femoral head cartilages at the chondrolabral transitional zone of the mid-sagittal plane. The 12-month change in separate acetabular and femoral head cartilage ROIs at the chondrolabral transitional zone will be analysed as a secondary outcome. In addition, the 12-month change in standardised dGEMRIC z-scores for the acetabular and femoral head cartilage ROIs at the chondrolabral junction will be analysed, using the central femoral cartilage ROI as an internal control [31, 32]. The dGEMRIC technique has been proven reliable for quantification and detection of changes in the glycosaminoglycan (GAG) content of the hip joint cartilage [33–36]. Since the loss of GAG in cartilage is an early OA-related change [37], dGEMRIC enables the likelihood of future OA development to be compared between treatment methods after a relatively short period. Further detail regarding the dGEMRIC outcome measurements and analyses is included below.

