The primary analysis will be of the change in the dGEMRIC index score for a combined acetabular and femoral head cartilage ROI from baseline to 12 months, with the difference in mean change between the two treatment groups presented with a 95% confidence interval and compared using an independent samples t-test. This strategy will also be applied for the standardised dGEMRIC z-scores. Change in scores for the dGEMRIC data will be assumed to be normally distributed; possibly after appropriate variance-stabilising transformation of the individual time-point scores. Analysis including adjustment for baseline dGEMRIC index score and relevant baseline characteristics will be performed using Analysis of Covariance with the change from baseline modelled as the dependent variable. This strategy will also be applied for the dGEMRIC index score of the separate acetabular and femoral head cartilage ROIs and the standardized dGEMRIC z-scores.

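### The 90% power rests on an SD described as that of the dGEMRIC index, but the primary test is on 12-month change, so the stated power depends on an unstated baseline to 12-month correlation

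*Protocol article*

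**What the plan says.** In the Protocol article, the Sample size section sets 90% power and a two-sided 5% level, and arrives at 54 per arm. The target effect is worded as follows: "we expect to detect a difference of at least 50 ms between two study groups at 12 months". The spread assumed for that target is attached to the index, not to its change: "based on a standard deviation (SD) of 80 ms for the dGEMRIC index". With the allowance for drop-out, the target is 140 participants.

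The Outcomes section defines the endpoint as a change: "The primary outcome measure for analysis will be the 12-month change in the average T_1_ relaxation time". The Statistical analysis section (under Descriptive analysis) agrees: "The primary analysis will be of the change in the dGEMRIC index score". The two arms' mean changes are to be compared with an independent samples t-test. An ANCOVA of change that adjusts for the baseline index and other baseline characteristics comes after the t-test, as a further analysis.

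**The concern.** The SD that matters for power is the SD of the variable tested. The Sample size section attaches 80 ms to the index, whereas the analysis section tests change in the index. The analysis section itself separates change scores from the scores at individual time points, so the natural reading of an SD for the index is a time-point SD.

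The two SDs coincide only at one value of the correlation between visits. If the correlation is lower, the change score is noisier than 80 ms and the headline power for the primary outcome is too high. If it is higher, the headline power is too low. The article states the sample-size inputs and the primary test side by side without linking them, so a reader cannot tell which case applies. This matters for interpretation, because the analysis section says the main analyses are expected to give definitive results.

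**Working it through.** **Inputs from the article.** Difference 50 ms; SD 80 ms; two-sided 5%; power 90%; 54 per arm (Sample size). 1:1 allocation (Trial design). 140 recruited less 20% leaves 112, or 56 per arm.

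**Inputs assumed.** The article gives no ρ, so a range is shown. The SD is taken as 80 ms at both visits.

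**Step 1: reproduce the stated figure.** The normal formula gives

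n per arm = 2 × (1.96 + 1.2816)² × (80/50)² = 2 × 10.508 × 2.56 = 53.8, rounded up to 54.

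Power at 54 per arm is 90.1% by the normal approximation and 89.6% by the noncentral t. The arithmetic is therefore sound, provided that 80 ms is the SD of the variable tested.

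**Step 2: SD of change when 80 ms is a time-point SD.**

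Var(change) = 80² + 80² − 2ρ·80², so SD of change = 80·√(2(1−ρ)). This equals 80 ms at ρ = 0.5.

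**Step 3: power and sample size of the t-test on change.** The required n is 53.8 × 2(1−ρ), rounded up. For example, at ρ = 0.3 it is 53.8 × 1.4 = 75.3, hence 76. Power is by the noncentral t.

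| ρ | SD of change (ms) | Power, 54 per arm | Power, 56 per arm | n per arm for 90% |
|---|---|---|---|---|
| 0.2 | 101.2 | 72.0% | 73.6% | 87 |
| 0.3 | 94.7 | 77.6% | 79.1% | 76 |
| 0.4 | 87.6 | 83.6% | 84.9% | 65 |
| 0.5 | 80.0 | 89.6% | 90.6% | 54 |
| 0.7 | 62.0 | 98.6% | 98.8% | 33 |

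**Step 4: break-even correlation (normal formula).** Setting 53.8 × 2(1−ρ) equal to n gives ρ = 1 − n/107.6. That is 0.50 at 54 per arm, 0.48 at 56, and 0.35 if all 70 per arm are analysed.

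**Step 5: the ANCOVA already planned.** With the baseline index as covariate, the residual SD is 80·√(1−ρ²), which is never above 80 ms. Its variance relative to the change score is (1−ρ²) / (2(1−ρ)) = (1+ρ)/2, which is at most 1. Power at 54 per arm by the normal approximation is 90.1% at ρ = 0, 92.6% at 0.3, 94.3% at 0.4, 96.3% at 0.5 and 99.5% at 0.7. The noncentral t gives 89.6% at 54 and 90.6% at 56 for an SD of 80 ms, which is the worst case for ρ ≥ 0 apart from the one degree of freedom spent on the covariate.

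**The case against.** Much can be said for the plan, and most of it stands.

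- **The calculation is not wrong.** 54 per arm follows from the stated inputs. What is in doubt is what one input refers to.
- **80 ms may be the SD of change.** The section says its calculation is for the primary outcome, which is a change. The sources cited for the SD are not available here. If they report an SD of change, 54 per arm stands and one phrase settles the point.
- **The 50 ms target fits either analysis.** Under randomisation the expected difference in mean change equals the expected difference at 12 months, so the reference to 12 months does not by itself make the comparison cross-sectional. Only the SD is in question.
- **The full protocol or the SAP may give a correlation.** For that reason the point does not rest on its absence from a condensed article. It rests on the article stating an SD for one quantity and a test on another.

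A reader might go further and infer that the trial is underpowered and that a null result would be over-read. The documents do not support that. They report no ρ, and their indirect evidence points both ways. The small region of interest, the two permitted contrast agents and the variable time from surgery to the 12-month scan could lower the correlation or widen the spread of change. The same scanner at both visits, averaging over three slices, stable person-level influences on T1 and the reliability claimed for the technique could raise it.

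**Conclusion.** The point holds in a conditional form. If 80 ms is a time-point SD, equal at both visits, the 90% power stated for the primary test requires ρ of about 0.5 or more at 54 per arm. Below that, power falls to 84% at 0.4, 78% at 0.3 and 72% at 0.2. Above it, the trial has more power than claimed. Neither the value of ρ nor the nature of the 80 ms is settled by the article, so a shortfall is possible but not demonstrated.

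The treatment estimate and its confidence interval remain valid whatever ρ is; what is unsupported is the link between the power claim and the test named as primary. This should be fixed, because it concerns the headline power for the primary outcome, but it is not a fault that must be cured before the trial can be relied on.

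**What to change.** Preferred: name the baseline-adjusted ANCOVA as the primary analysis, keep the unadjusted t-test on change as supportive, and tie the power statement to the ANCOVA. If 80 ms is the time-point SD, 54 to 56 per arm then gives about 90% power or more for any ρ ≥ 0. Precision is never worse than that of the t-test on change, beyond the loss of one degree of freedom.

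Alternative, if the t-test on change stays primary: state that 80 ms is the SD of change, if the sources bear that out. Otherwise restate the power of that test over a range of ρ, for example 0.3 to 0.7, with the equal-SD assumption made explicit.

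The preferred change costs a short edit to the Sample size and Statistical analysis sections and no extra patients. Under the alternative, the stated power may turn out lower than 90% over part of the range.

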**Methods:**

This is a pragmatic, multi-centre, two-arm superiority randomised controlled trial comparing hip arthroscopy to physiotherapy-led management for FAI. A total of 140 participants with FAI will be recruited from the clinics of participating orthopaedic surgeons, and randomly allocated to receive either surgery or physiotherapy-led non-surgical care. The surgical intervention involves arthroscopic FAI surgery from one of eight orthopaedic surgeons specialising in this field, located in three different Australian cities. The physiotherapy-led non-surgical management is an individualised physiotherapy program, named Personalised Hip Therapy (PHT), developed by a panel to represent the best non-operative care for FAI. It entails at least six individual physiotherapy sessions over 12 weeks, and up to ten sessions over six months, provided by experienced musculoskeletal physiotherapists trained to deliver the PHT program. The primary outcome measure is the change in dGEMRIC score of a ROI containing both acetabular and femoral head cartilages at the chondrolabral transitional zone of the mid-sagittal plane between baseline and 12 months. Secondary outcomes include patient-reported outcomes and several structural and biomechanical measures relevant to the pathogenesis of FAI and development of hip OA. Interventions will be compared by intention-to-treat analysis.

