The above strategy will also be performed for analysis of other approximately normally distributed secondary outcome measures including those related to plain radiography, MRI, muscle strength, full 3D gait analyses, EMG-informed NMS and FEM models, and the patient reported outcomes (iHOT-33, HOOS, EQ-5D and SF-12). Differences in dichotomous outcome variables such as adverse events, complications related to the trial interventions and the need for further procedures will be compared between groups using chi-squared tests (or Fisher’s exact test). The temporal patterns of complications and the need for further procedures will be presented graphically. If there are sufficient events cumulative incidence curves of the time to first procedure (any or a specific type) will be plotted by treatment group calculated using the Kaplan-Meier method. Ordinal scores for patient satisfaction will be compared between intervention groups using proportional odds logistic regression analysis with the proportional odds assumption checked. Although our inferences will be drawn from the intention-to-treat analysis, we will perform per protocol analyses to place these in context. We plan to perform exploratory subgroup analyses by FAI type and by whether referral to the study was via the private or public healthcare systems. We do not anticipate that crossovers will be a major issue for this study. We, therefore, expect the main analyses to provide definitive results. If participant adherence to or completion of the PHT proves to be more problematic than expected, we will augment the planned analysis with a complier average causal effect (CACE) analysis.

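### Crossover to surgery is budgeted as drop-out, but under intention to treat it dilutes the difference; power is about 85–90%, depending on the unstated base of the 5%

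*Protocol article*

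**What the plan says.** The Sample size section of the protocol article sets 90% power at a "two-sided significance of 5% significance level". The aim of the calculation is worded as follows: "we expect to detect a difference of at least 50 ms between two study groups at 12 months". The assumed SD is 80 ms, and 54 patients per arm are said to suffice. A second calculation, relating cartilage loading to dGEMRIC, asks for 56. The recruitment target of 140 is then set "to allow for a drop-out rate of 20%, including 5% cross over to the surgical group".

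On the analysis, the abstract says "Interventions will be compared by intention-to-treat analysis", and the Statistical analysis section says "our inferences will be drawn from the intention-to-treat analysis", with per-protocol analyses only for context. That section also expects crossover not to be a major problem. It reserves a complier average causal effect analysis for the case where PHT adherence or completion is worse than expected. The MRI section has every participant scanned at baseline and at 12 months.

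The article does not say whether the 5% is a share of all participants or of the PHT arm, and it does not reduce the 50 ms for crossover.

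**The concern.** Drop-out and crossover act differently on an intention-to-treat comparison. A patient lost before the 12-month scan lowers the number analysed and leaves the expected difference alone, if the loss is uninformative. A PHT patient who has surgery and is scanned stays in the PHT mean and pulls it towards the surgical mean. The number analysed is unchanged, but the expected difference falls. Dividing by 0.80 corrects for the first mechanism only. Putting crossover inside that 20% removes patients whom the analysis will keep and omits the dilution they cause.

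What is at stake is the power quoted for the primary comparison. The planned test is the intention-to-treat t-test, and the stated 90% is not derived for that test in the presence of the crossover that the same section allows for.

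**Working it through.** **Inputs.** From the Sample size section: difference 50 ms, SD 80 ms, two-sided alpha 0.05, power 90%, 54 per group, second requirement 56, target 140, total allowance 20% including 5% crossover. From Trial design: 1:1 allocation, so 70 per arm. From Statistical analysis: independent-samples t-test on mean change, intention to treat.

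**Step 1: the plan's own figures.**
- n per group = 2 × (1.960 + 1.282)² × 80² / 50² = 53.8, rounded up to 54. This reproduces.
- Power with 54 per group and 50 ms: 90.1% by normal approximation, 89.6% by noncentral t.
- 2 × 54 / 0.80 = 135, and 2 × 56 / 0.80 = 140. The article does not show this step, but the second expression gives its target.
- If all 20% are removed, 56 per arm remain, and power for 50 ms is 91.1% (normal) or 90.6% (t).

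**Step 2: separate loss from crossover.** True loss is 20% − 5% = 15%. Analysed: 140 × 0.85 = 119, or 59.5 per arm if losses are equal. The standard error of the difference is 80 × √(2/59.5) = 14.67 ms.

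**Step 3: dilute the difference.** If a share c of the PHT arm obtains the full surgical effect, the expected intention-to-treat difference is 50 × (1 − c). Approximate power is Φ(difference / 14.67 − 1.960).

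| Base of the 5% | Crossovers | c | Difference | Power, normal | Power, t |
|---|---|---|---|---|---|
| PHT arm | 3.5 of 70 | 5.0% | 47.5 ms | 89.9% | 89.5% |
| PHT arm, all crossovers scanned | 3.5 of 59.5 | 5.9% | 47.1 ms | 89.4% | 88.9% |
| All 140 | 7 of 70 | 10.0% | 45.0 ms | 86.6% | 86.1% |
| All 140, all crossovers scanned | 7 of 59.5 | 11.8% | 44.1 ms | 85.3% | 84.7% |

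Worked line for the third row: 45 / 14.67 = 3.07; 3.07 − 1.96 = 1.11; Φ(1.11) ≈ 0.866.

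The seven crossovers in the last two rows must all come from the 70 PHT patients, because crossover is defined as movement to surgery. That is why 5% of the trial becomes 10% of one arm.

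**Step 4: sensitivity.** The SD is held at 80 ms. Adding the extra variance of a PHT arm that mixes two means lowers these powers by at most about 0.7 points. By normal approximation, power at 59.5 per arm reaches exactly 90% when c is about 4.9%.

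**The case against.** Four points on the other side carry weight.

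- **The size of the shortfall depends on the base of the 5%.** A reader might infer that crossover takes power clearly below 90%. If the 5% refers to the PHT arm, it does not: 89.5% by t-test compares with 89.6% for the planned 54 per group. Two things offset the dilution. The target of 140 exceeds the 135 needed for 54 per group, and keeping crossovers raises the analysed number from 56 to 59.5 per arm. This stands, and it is why the result is a range.
- **The 50 ms may already be the difference between randomised groups.** The article speaks of two study groups, which can be read as the intention-to-treat contrast. No dilution is then due, and 59.5 per arm gives 92.2% by t-test. This also stands as a possible reading, so the lower figures are conditional on 50 ms being the effect of treatment received.
- **Full dilution is an upper bound.** PHT can run to six months, so surgery after crossover could come late in the year. The dGEMRIC section notes that surgical trauma has been suggested to lower T1 for a time. A late crossover may show only part of the surgical effect, or none, by 12 months.
- **The plan's arithmetic is right.** Both 54 and 140 reproduce. The fault is the choice of adjustment.

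A reader might also infer from the word drop-out that crossovers will be left out of the primary analysis. Nothing in the article says so: inference is from intention to treat, and per-protocol results are only context. Nor should a full 20% loss be combined with dilution, because the 20% already includes the crossover and the combination would count it twice.

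**Conclusion.** The sample-size section makes the wrong adjustment for crossover, given the analysis the article names. It subtracts patients who will be analysed and leaves undiluted a difference that they would shrink. This holds whichever base the 5% has.

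The consequence for power is modest. With 140 recruited and 15% true loss, it is about 85–86% if the 5% refers to all participants, and about 89–90% if it refers to the PHT arm. The first is the more literal reading, because the 20% containing the 5% is applied to the 140; the second is essentially the planned power. Both rest on 50 ms being the effect of treatment received, full surgical effect in every crossover, equal loss in the two arms, and an SD of 80 ms. Weaker or later effects in crossovers would bring power closer to the undiluted figure.

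The documents do not support a flat statement that power is below 90%, nor a claim that crossovers will be excluded.

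**What to change.** Restate the last part of the Sample size section in three steps:

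1. Give 15% loss to follow-up and 5% crossover to surgery as separate allowances, and name the base of the 5% (all participants or the PHT arm).
2. Say whether 50 ms is the effect of treatment received or the difference between randomised groups. If it is the former, give the diluted intention-to-treat difference (about 47.5 ms for the PHT-arm base, about 45 ms for the whole-trial base) and the resulting power with 140 recruited (about 85–90%).
3. State that crossovers are analysed in the arm to which they were randomised and are not counted as drop-outs.

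The cost is a rewording and a slightly less favourable stated power. The restatement needs no extra patients and no change to the primary analysis.

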### Data safety and monitoring

An independent Data Safety and Monitoring Board (DSMB) will be responsible for oversight of this clinical trial, including protocol adherence, recruitment, adverse events, SAEs, treatment side effects and data analysis and data safety. The members of the DSMB are not involved in the study, do not have any conflict of interest and will not benefit in any way from the results of this trial.

